#### Transplant centre’s data collection

A representative of the transplant service, indicated by the centre’s manager, enters the data from the questionnaire directly into Red Cap system.

Data collection began on December 7, 2015, and is planned for 18 months, with expected completion in June 2017. The quality of the information registered into the RedCap system of each centre is verified by the central study coordinators on a weekly basis, ensuring that there is no missing data or errors in data entry, and reports of found inadequacies are regularly, once a week, reported to each centre. Once data collection is completed, a summary report of adherence rates and factors associated with non-adherence will be provided to each centre. After completion of the study, a benchmark report will be sent to each transplant centre, in which the results of each will be summarized and compared to the data from other centres. Only the information of the centre receiving the report will be individualized, with the data from other centres presented in pooled and anonymized manner.

### Statistical analysis plan

#### Aim 1

In addition to the general prevalence estimates of non-adherence to health behaviours, the adopted sample design allows for stratified estimates to be calculated according to region (South/Southeast, North/Midwest/Northeast), the activity level of the transplant centre, and the sample strata. Prevalence estimates will be presented as percentages, with their respective 95% confidence intervals (95% CI), calculated using Taylors’ Linearization Series given the multistage sampling design of the study. For numerical variables with a normal distribution, the mean and respective 95% CI will be calculated and for variables with significantly skewed distribution, the median and inter-quartile interval. Box-plots and normal probability plots will be used to assess the distribution properties. Graphics will be used, where relevant, to enhance visualization, including grouped box-plots and bar plots for prevalence.

#### Aim 2

To explore the association between medication non-adherence and multilevel studied correlates, the analyses will follow the multilevel ecological model, following the hierarchical approach [70]. This approach is a forward driven variable selection method, based on the epidemiological framework adopted, following the proximity of the variable levels to the patient in a theoretical causal framework. The non-adherence indicator (binary) variable will be analysed using generalized estimation equations (GEE). This population average approach is an adequate modelling framework that can handle the multistage nature of the study design, as well as provides flexibility regarding the probability distribution adequate to each outcome variable nature, and consequently the association parameter to be estimated. For instance, binary outcomes, such as non-adherence, will be modelled using the Poisson distribution and the log link function, providing prevalence ratios as association parameter. Discrete or count outcomes, like absence at scheduled follow-up consultations, can also be modelled as a Poisson or Negative Binomial distribution with log link function, but providing a counting rate ratios as the association parameter. Association effects will be considered of scientific relevance on the basis on their magnitude (effect size), precision (by their 95% CI) and associated *p*-value. As per the recent statement from the American Statistical Association, terms such as ‘statistically significant and model adjustment based only on p-values’ will no longer be adopted in the analysis [71].

All analyses will be performed using IBM Statistics (SPSS 24.0, Chicago, IL, USA) and STATA (version 14, StataCorp LP, College Station, TX, USA) statistical packages. All codes used will be publically available, permitting reproducibility.

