### Sampling design and setting

A convenience sample of 20 centres was identified for inclusion, using a stratified sampling strategy. In Brazil, the KT activity of a centre is strongly associated with its geographical regions and its regional economic development. High activity centres are concentrated in the South and Southeast regions of the country, with low/moderate activity centres being more prevalent in the North, Northeast, and Midwest regions. To ensure an adequate representativeness from the enrolled centres, we defined four strata of equal size (approximately 283 patients): North, Northeast and Midwest with low or moderate activity; South and Southeast with low activity; South and Southeast with moderate activity; and South and Southeast with high activity. In each stratum, the number of patients in each centre is proportionally defined by the number of patients being followed up. The inclusion criteria for centres were as follows: performance of ≥10 KTs per year over the 5-year period preceding the study (2010-2014) and a signed agreement provided by the centre’s director. The 20 centres participating in the study are listed in Table 1, with their geographical distribution shown in Fig. 2. The majority of centres were located along the coast, following the same distribution as large- and medium-sized Brazilian cities [48].

**Table 1 Tab1:** Participating centres of the ADHERE BRAZIL Study, divided by Brazilian geographical regions and transplant activity

Centre	Brazilian region	Transplant activity ^a^
Hospital Ophir Loyola – Belém/PA	North	Low
Hospital Universitário do Maranhão – São Luiz/MA	Northeast	Low
Hospital Antônio Targino Ltda. - Campina Grande/PB	Northeast	Low
Hospital Universitário Onofre Lopes - Natal/RN	Northeast	Low
Hospital Universitário Walter Cantídio – Fortaleza/CE	Northeast	Moderate
Hospital Universitário de Brasília – Brasília/DF	Midwest	Low
Centro Estadual de Transplantes/Hospital São Francisco de Assis na Providência de Deus - Rio de Janeiro/RJ	Southeast	Moderate
Fundação IMEPEN/Hospital Universitário da Universidade Federal de Juiz de Fora – Juiz de Fora/MG	Southeast	Low
Fundação Osvaldo Ramos - Hospital do Rim e Hipertensão/UNIFESP – São Paulo/SP	Southeast	High
Hospital Israelita Albert Einstein – São Paulo/SP	Southeast	Moderate
Hospital São João de Deus – Divinópolis/MG	Southeast	Low
Hospital das Clínicas da Universidade Estadual de Campinas/Unicamp – SP	Southeast	Moderate

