The number of patients included by each centre, considered as clusters in the analysis, is proportional to the number of transplants performed per year and the number of patients in follow-up, so called the size of the KT centre. According to the RBT 2012, there were 123 active transplant centres in Brazil, distributed across 22 states, which performed 5385 KTs in that year [49]. Due to the absence of an official classification of KT centres based on their activity, we proposed the following classification, which is based on a pre-existing classification for heart transplantation [18], and taking into consideration the profile of the centres included in the study: low activity, ≤50 KTs/year; moderate activity, 50-150 KTs/year, and high activity, ≥150 KTs/year. We used the 5 years prior to the study period (2010 to 2014) as the reference period for the KT activity of a centre. Our classification was validated by consulting specialists through a web survey, with 92% of respondents considering our proposal as either ‘adequate’ or ‘very adequate’.

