#### Multilevel correlates of non-adherence to immunosuppressive medication

##### Patient level

Demographic (age, sex, race, education, employment status, marital status, family income), disease related (aetiology of kidney disease, treatment modality prior to transplant, preemptive transplant, time on dialysis, donor type, post-transplant time, comorbidity, height, weight), and therapy related data (drugs of immunosuppressive schema, number of immunosuppressive medications, daily number of doses of immunosuppressants) are collected through structured interview and review of charts [20, 26, 58–61]. The following post-transplantation clinical data is collected from medical charts: number of treated acute rejection episodes, creatinine level, estimated glomerular filtration rate, and re-hospitalizations [52, 61–64] (Additional file 1: Table S2).

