The use of a consistent methodology of non-adherence to medication measurements will provide an accurate prevalence and allow us to conduct reliable comparisons between centres, regions, and clinical practice patterns. Our sampling methodology tried to avoid selection bias of patients, given that the centres were selected by convenience. Recruiting centres from all regions, and then including different patterns of clinical practice, administration and transplant activity, and a randomized selection of patients, will increase the reliability of the study findings to Brazil and to other countries with similar health systems. The multilevel analysis of factors associated with non-adherence, including at the level of the patient, healthcare provider, health care organization, health care system and policies, will enable us to capture a wide range of factors correlated to non-adherence. Furthermore, we believe that the identification of the clinical practice patterns positively associated with adherence might be the most valuable potential contribution of this study, and such practices can be promptly adopted in KT care. This information, for the first time involving a large sample of KT patients, will provide an accurate view of the current state of non-adherence after KT, and identify targets for further interventions. Data collection using the RedCap system promotes a constant and ongoing quality surveillance of included data. The RedCap system provides a useful tool for collecting data across multiple centres and for problem solving, at a distance, which is essential considering that our study covers a territory of 328,804 mi^2^ and 200 million inhabitants. As another relevant point, we will provide feedback to each centre regarding their patients’ adherence behaviours, which the centres can use to improve their clinical practice.

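### With only 20 centres as clusters, the planned Poisson GEE needs a small-sample correction; without one, robust intervals for factors constant within a centre are too narrow

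*Protocol article*

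**What the plan says.** - **Model.** Statistical analysis plan, Aim 2: "The non-adherence indicator (binary) variable will be analysed using generalized estimation equations (GEE"). Binary outcomes "will be modelled using the Poisson distribution and the log link function, providing prevalence ratios as association parameter". The same section describes the population-average approach as adequate for the multistage design. It judges associations jointly on effect size, 95% confidence interval and p-value. Variables enter by a forward, hierarchical selection that follows the ecological model.
- **Clusters.** Sampling design and setting describes the centres as "considered as clusters in the analysis". Their number is fixed: "A convenience sample of 20 centres was identified for inclusion, using a stratified sampling strategy".
- **Centre-level factors.** The meso-level variables come from one questionnaire per centre, completed by a nominated nurse or physician. Transplant activity and region are properties of the centre. City resources are shared by every patient of a centre.
- **Weight given to them.** The Discussion says that "identification of the clinical practice patterns positively associated with adherence might be the most valuable potential contribution of this study", and adds that such practices could be adopted promptly. Each centre is also to receive a report on the factors associated with non-adherence.
- **Not stated.** The article names no variance estimator, working correlation, small-sample correction or reference distribution.

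**The concern.** The robust (sandwich) variance in GEE is justified by a large number of clusters. The patient count does not help a covariate that takes one value per centre: its information comes from 20 units, however many patients each contributes. With so few clusters the uncorrected sandwich is biased downward and the normal reference is too light-tailed. Both errors make intervals too short.

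The model choice makes this matter. A Poisson model for a binary outcome misstates the variance, so the analysis leans on the robust variance to be usable. That variance is weakest for the practice-pattern results to which the Discussion gives most weight. At stake is that centre practices with no association would be reported as associated too often, and then fed back to centres.

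**Working it through.** **1. The plan's own figure.** Inputs from Sampling design and setting: population 31,241, prevalence 0.50, error 0.05, 95% confidence, design effect 3.0.

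n = DEFF × N p(1−p) / [(d²/z²)(N−1) + p(1−p)] = 3 × 7810.25 / (20.33 + 0.25) = 3 × 379.5 = 1138.5, so 1139. This matches the article.

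**2. Intraclass correlation implied by the plan.** Mean centre size = 1139/20 = 56.95. ICC = (3 − 1)/(56.95 − 1) = 0.036. This treats centres as equal in size; the range 0.01 to 0.10 was also tried.

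**3. Layout.** "we defined four strata of equal size (approximately 283 patients"). By Table 1 the strata hold 6, 6, 4 and 4 centres, so about 283/6 = 47 or 283/4 = 71 patients per centre. High activity is 4 centres against 16. City variables take at most 20 − 2 − 1 − 1 = 16 distinct values (three centres in São Paulo, two each in Juiz de Fora and Porto Alegre).

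**4. Why a robust variance is needed.** At 50% prevalence the Poisson variance is 0.50, while the binary variance is 0.50 × 0.50 = 0.25. Model-based standard errors for patient-level factors are therefore about √2 = 1.4 times too large. In simulation, the unscaled model-based version rejected a null centre factor only about 2–3% of the time with up to five centre terms. It is not a correct substitute either.

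**5. Simulation.** Poisson/log GEE, 20 centres, prevalence 0.5, ICC 0.036, no true effect. False-positive rate at nominal 5%:

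| Centre-level terms | Uncorrected, z (2,000 runs) | Uncorrected, z (separate 600 runs) | Bias-corrected, t on 20 − p (same two sets) |
|---|---|---|---|
| One, 10 v 10 | 8.1% | 8.3% | 4.1%, 4.2% |
| One, 4 v 16 | 11.9% | 11.2% | 5.8%, 6.7% |
| Five | 15.1% | 13.7% | 2.9%, 2.7% |
| Eight | 21.9% | 19.2% | 1.0%, 1.7% |

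The correction in the 2,000-run set is Mancl-DeRouen. A further set gave about 8%, 14% and 20% for the first, second and fourth rows uncorrected, and 5–9% with Kauermann-Carroll and t.

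**6. Coverage and width.** 4,000 runs per scenario, including unequal centre sizes (25 to 148, assumed) and ICC 0.01 to 0.10. Coverage of the uncorrected 95% interval:
- one 10/10 factor: 0.91–0.93;
- one 4/16 or continuous factor: 0.85–0.89;
- three further centre terms: 0.81–0.89;
- six further centre terms: 0.77–0.84.

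Results barely change with the ICC. Corrected coverage is 0.91–0.96 (Kauermann-Carroll with t) and 0.94–0.98 (Mancl-DeRouen with t). Uncorrected width relative to Kauermann-Carroll with t is 0.82–0.89 for one centre covariate (11–18% narrower) and 0.65–0.69 with six further (31–35% narrower).

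Simple K/(K−1) scaling with t is not enough. For 4 v 16 with unequal centres, ICC 0.036 and exchangeable correlation, coverage is 0.862 uncorrected, 0.891 scaled with t, 0.907 Kauermann-Carroll and 0.935 Mancl-DeRouen.

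**7. Patient-level factors.** Uncorrected coverage is 0.94 (1,500 runs), close to nominal.

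**The case against.** The strongest reply is that the article never says it will use an uncorrected sandwich. It is a condensed account, and a variance correction is a detail that a fuller analysis plan may hold. That stands: a reader might infer that uncorrected standard errors were chosen, and the text does not support it. What remains is that the article positively calls GEE adequate for this design. With 20 clusters that is true for centre-level factors only if a correction is added, and neither the uncorrected robust version nor the unscaled model-based version gives correct error rates.

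Other limits also stand:
- **Far too narrow.** This fits only many centre terms fitted jointly, and the article does not say how many will enter. For a single factor the shortfall is modest.
- **Singular covariance.** The Patient level section lists 23 variables, starting with "age, sex, race, education, employment status, marital status, family income". A reader might infer a full model with more parameters than centres, whose robust covariance would be singular. That is a list of data collected; forward selection may never fit such a model.
- **Capping all covariates.** Coverage of about 0.94 for a patient-level factor gives no reason to limit patient-level adjustment.
- **Certain false findings.** Even the worst scenario is 22%. Aim 2 is exploratory, p-values are not to be used alone, and the article says causality cannot be inferred. Its 95% intervals nevertheless carry the same error as its p-values.
- **Scope.** Trust, satisfaction, social support and insurance status vary between patients within a centre, so the problem does not extend to all micro- and macro-level correlates.

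**Conclusion.** The point holds in conditional form. With 20 centres, an uncorrected robust analysis gives intervals that are too short for factors constant within a centre. False-positive rates are about 8% for one balanced factor, 11–14% for a 4-versus-16 factor such as high activity, and about 14–22% with five to eight joint centre-level terms, against a nominal 5%. The error is modest to substantial, depending on balance and on the number of centre terms. Patient-level results are almost untouched.

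The number of centres, the clustering, the model, the prevalence and the design effect are the article's own. The assumptions are the use of an uncorrected robust variance with a normal reference, the ICC (0.036 implied, 0.01 to 0.10 tried), centre sizes within strata, the covariate distributions and the number of centre-level terms. The null simulations do not include the forward selection step.

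**What to change.** Keep the GEE with Poisson distribution and log link. For factors constant within a centre, state that 95% intervals and p-values use a small-sample bias-corrected robust variance. The t reference should have degrees of freedom equal to 20 minus the number of centre-level parameters, counting the intercept (18 for one single-term factor).

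Kauermann-Carroll is a reasonable choice but still runs up to about 9% false positives in the simulations. Mancl-DeRouen holds the level better for the 4-versus-16 contrast but is conservative with many terms (1–3% with five to eight). For that reason, fit only a few centre- or system-level terms at a time. Do not cap patient-level covariates.

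The cost is a change of analysis text and an add-on routine, with no new patients or data. Against the uncorrected version, Kauermann-Carroll intervals are about 1/0.89 = 1.12 to 1/0.82 = 1.22 times as wide for a single centre factor. With six further centre terms they are about 1/0.69 = 1.45 to 1/0.65 = 1.54 times as wide.

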### Ethical considerations

The study was reviewed and approved by the ERB of University Hospital of Federal University of Juiz de Fora (691.120), and nationally registered (CAAE 27972914.1.1001.5133). All participating centres also locally submitted the protocol to ERB approval before data collection. Information and informed consent followed the guidelines of the Declaration of Helsinki (World Medical Organization 1996) and specific national legislations. Written informed consent will be obtained from all the participants before the data collection.

## Discussion

By using appropriate methodology, our study will provide a broad and more representative information regarding non-adherence among KT patients in Brazil. Furthermore, we will also identify factors associated with medication adherence, especially at the level of health care service and health care team, which could provide potential leverage points for developing further interventions. This is the first multi-centre study that is assessing adherence and multilevel correlates in KT patients and in Brazil, which has a universal and public health care system and a territorial varsity. The social and economic diversity across the country, which mirrors the variation in the availability and access to health care, offers a unique opportunity to explore non-adherence. It is one of the few studies assessing patient non-adherence to the different aspects of the post-KT treatment, including: medication intake, alcohol and smoking cessation, physical activity and appointment keeping in a large KT population.

The use of a consistent methodology of non-adherence to medication measurements will provide an accurate prevalence and allow us to conduct reliable comparisons between centres, regions, and clinical practice patterns. Our sampling methodology tried to avoid selection bias of patients, given that the centres were selected by convenience. Recruiting centres from all regions, and then including different patterns of clinical practice, administration and transplant activity, and a randomized selection of patients, will increase the reliability of the study findings to Brazil and to other countries with similar health systems. The multilevel analysis of factors associated with non-adherence, including at the level of the patient, healthcare provider, health care organization, health care system and policies, will enable us to capture a wide range of factors correlated to non-adherence. Furthermore, we believe that the identification of the clinical practice patterns positively associated with adherence might be the most valuable potential contribution of this study, and such practices can be promptly adopted in KT care. This information, for the first time involving a large sample of KT patients, will provide an accurate view of the current state of non-adherence after KT, and identify targets for further interventions. Data collection using the RedCap system promotes a constant and ongoing quality surveillance of included data. The RedCap system provides a useful tool for collecting data across multiple centres and for problem solving, at a distance, which is essential considering that our study covers a territory of 328,804 mi^2^ and 200 million inhabitants. As another relevant point, we will provide feedback to each centre regarding their patients’ adherence behaviours, which the centres can use to improve their clinical practice.

Our study has certain limitations. First, although the 20 centres included in the study were representative of different kinds of centres and regions of Brazil, these centres were selected and recruited by convenience, which allowed our study to be economically feasible and to achieve a potential low dropout rate. Although centres were selected by convenience, patients were randomly selected. Second, due to limited resources, it was not possible to evaluate non-adherence to immunosuppressants using electronic monitoring. We opted to apply a combination of diagnostic methods [27], (i.e. patient self-report, collateral report from nurse/physician, and immunosuppressive blood levels) which has previously been shown to provide the highest sensitivity compared to electronic monitoring [29]. Our evaluation of the CIM model is limited but, to our knowledge, this will be the first time that this model is being evaluated within the context of KT. Finally, as a cross-sectional study, causality between identified factors and non-adherence to post-KT treatment cannot be inferred.

In conclusion, the ADHERE Brazil study is a cross-sectional study evaluating various aspects of non-adherence behaviour to the treatment regimen, and multi-level correlates to immunosuppressive medication non-adherence in 1130 patients across 20 KT centres. Data from this study will provide evidence to people involved in treating KT patients (health care professionals, health care policy makers) regarding the level (patient, health care professional, and health care system and policies) at which further interventions should be implemented to improve adherence to the post-KT treatment and, consequently, the long-term outcomes.

